**Methods:**

A double blind, randomized controlled trial will be used in this study to examine the effectiveness of App-based CBT in reducing the prevalence of postpartum depression compared with usual postpartum care in China. A total of 120 participants will be recruited in this study. The intervention consists of a weekly theme module app for continuous six weeks, each module including learning content and assignments. The control group received usual postpartum care content through the App. Outcome measures include postpartum depression, anxiety, pressure and parenting sense of competence at 0-, 3- and 6-month after the intervention.

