### Participants

This study will be conducted in Changsha city, which has five administrative district. We will randomly select one health center from all the community health centers in each district. Participants will be recruited from five community health centers we selected. Inclusion criteria:has Established maternal health care record in community health centers;0 days to 6 weeks after delivery;Score of 9–12 on the Edinburgh Postnatal Depression Scale (EPDS);Access to smart phone and able to independently use App;Informed consent and voluntary participation.

Exclusion criteria:Severe mental disorders (current or in the past);History of brain injury, intellectual disability or cognitive disorder; andUndergoing psychotherapy or any other psychological intervention.Patients diagnosed with postpartum depression or other severe mental illness during the study.

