### Measures

Measurements will be obtained at baseline (t_o_), immediately after the last intervention (t_1_), 3 months following the intervention (t_2_) and 6 months following the intervention (t_3_). The baseline data is collected when participants are enrolled, and after that, the data collection process will be implanted in the evaluation module of the mobile App. The primary outcome will be depression status. The secondary outcomes will be negative emotion symptoms including depression, anxiety and stress, parenting confidence. These will be measured as follows:*Demographic and Socioeconomic factors:* the information about Risk factors will be collected by demographic questioner including pregnancy and birth history, obstetric complications, delivery mode, baby gender, baby weight, baby health status, feeding pattern, satisfaction with family care, major life events. The socioeconomic factors include maternal age, marital status, history of depression, family history of mental disorder, occupation, medical insurance, education level, family income, and religious belief.*Depression status:* We will use the Edinburgh Postnatal Depression Scale (EPDS) Chinese version to assess participant’s depressive status, as this scale is an effective self-screening tool for PPD. The EPDS to be used in this study was translated by Lee [35] the sensitivity was 82%, the specificity was 86%, the positive predictive value was 44%, and the negative predictive value was 97%. The scale includes 10 items. The recommended threshold is < 9: no depression; 9 is regarded as a probable case; and 13 or more as suspected depression.*Negative emotion symptoms:* We will assess negative emotion symptoms using the Depression, Anxiety and Stress Scale (DASS-21), which is a self-report measure of anxiety, depression and stress levels used in diverse settings developed by Lovibond [36]. The Chinese version of DASS-21 was developed by Taouk ^[40]^ in 2001. This version was tested in Australian-Chinese speaking samples and Hong Kong-Chinese speaking samples, and indicated that the items had been adequately and appropriately translated and adapted. Wen Yi et al. [37] tested DASS-21 in 730 Chinese adults (over 18 years old), the result showed that the Cronbach’s α was 0.912 and the test-retest Pearson correlation coefficient was 0.751.*Parenting competence:* Parenting competence will be assessed using the Chinese version of Parenting Sense of Competence Scale (C-PSOC). The initial Parenting Sense of Competence Scale was an English version developed by Gibaud-Wallston [38]. In 2014 Chinese researcher, Yang Xiao translated it into Chinese and applied to Chinese population. C-PSOC includes efficacy and satisfaction factors and has 17 items. The Cronbach’s coefficient, efficacy factor and satisfaction factor of C-PSOC were 0.82, 0.80 and 0.85 respectively [39].

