### Sample size

A power analysis was performed for linear regression using University Dusseldorf G*Power 3.1 to determine the sample size necessary for analysis. The main objective of this study is to assess the effectiveness of App-based CBT on PPD high-risk mothers. According to previous studies, an effect size of 0.43 will be adopted [40]. The power analysis based on the conventional significant alpha level of 0.05 and a power of 0.90 using a two-tailed test. We calculate that the sample size required is 48 in each group. Considering a 20% dropout rate, the recruited sample size required in each group is 60.

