### Randomization

The allocation scheme is generated by the random digital program. The whole randomization process is a computer-based algorithm. The starting value will be determined by the current server time and the process of the allocation scheme will be recorded for replication. Randomization will not be stratified and will occur automatically at the completion of the baseline survey by obtaining the next allocation of the generated timeline.

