### Analysis

This study used double data entry. Data entrants, analysts, and data custodians do not participate in the intervention process. Analyses will be performed using SPSS (version 20.0; SPSS Inc., Chicago, Ill). All tests of significance will be determined at an alpha level of 0.05. The principle of ITT will be used to handle missing data. We plan to analyse contrasts between intervention and control groups at baseline, post intervention, 3 months and 6-months follow-up.

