### Risk management

In our study, participants have to complete EPDS at baseline, immediately after the intervention, three months after the intervention, and six months after the intervention. We will refer the participants to psychologist immediately after we found participants who had EPDS scores greater than 12. Each participant is entitled to withdraw from the study during the intervention, when they decided to withdraw from the study, our research team will assess their situation to see if they needed to be transferred to psychologist.

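### An exclusion for postpartum depression diagnosed during the study, read literally, removes randomised women after an event closely tied to the primary outcome, and nothing says they are retained

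*Protocol article*

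**What the plan says.** All references are to the protocol article.

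- **Participants**, last exclusion criterion: "Patients diagnosed with postpartum depression or other severe mental illness during the study". No time limit is attached. Entry requires an EPDS score of 9-12.
- **Randomization**: "Randomization will not be stratified and will occur automatically at the completion of the baseline survey".
- **Abstract, Methods**: the trial is "to examine the effectiveness of App-based CBT in reducing the prevalence of postpartum depression compared with usual postpartum care in China".
- **Measures**: the primary outcome is depression status on the EPDS, where "9 is regarded as a probable case; and 13 or more as suspected depression".
- **Risk management**: "participants have to complete EPDS at baseline, immediately after the intervention, three months after the intervention, and six months after the intervention". The same section adds: "We will refer the participants to psychologist immediately after we found participants who had EPDS scores greater than 12".
- **Analysis**: "The principle of ITT will be used to handle missing data". No analysis set is defined.
- **Sample size**: "Considering a 20% dropout rate, the recruited sample size required in each group is 60".

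**The concern.** An exclusion criterion should be checkable before allocation. This one cannot be, because the diagnosis it names can arise at any time up to six months after the programme. It is also closely linked to what the trial measures: a woman whose EPDS rises above 12 is sent to the professional who might make the diagnosis.

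If such women are then taken out, the women lost are those who did worst. If the App works, more of them come from the control arm, so the control arm looks better than it was and the contrast shrinks. Analysis cannot fully repair this, because the reason for loss is the outcome itself.

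**Working it through.** **Step 1. Timing, from the text.** Women enter with EPDS 9-12, so no eligible woman is above 12 at baseline. The next EPDS is at t1, after the last module, followed by t2 (3 months) and t3 (6 months). Referral triggered by the EPDS therefore starts at t1, when there is no App content left to stop. For those women the criterion either acts on follow-up or analysis, or does nothing. Only for a diagnosis reached by another route in weeks 1-6 could it mean stopping the App.

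**Step 2. Could it be an entry rule only?** The first exclusion already covers severe mental disorders, current or past. For other severe mental illness, the last criterion adds something only if it reaches beyond entry. For postpartum depression itself, an entry-only meaning is possible, but the words do not say so.

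**Step 3. Illustration of size.** The plan gives no figure to reproduce here. Inputs:

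- From the plan: effect size 0.43 (read as a standardised difference), 60 per arm, 48 after dropout.
- Assumed: follow-up EPDS normal, rounded and limited to 0-30; SD 4; control mean 9-10; correlation between visits 0.5-0.7; each woman above 12 at t1 or t2 diagnosed with probability 25-50%, the same in both arms, and removed from later visits. Measures reports a positive predictive value of 44% but ties it to no cut-off, so it is not used.

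*Referred at t1.* P(EPDS > 12) = 1 − Φ((12.5 − mean)/4). The intervention mean is the control mean minus 0.43 × 4 = 1.72.

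| Control mean | Control referred | Intervention referred |
|---|---|---|
| 9 | 1 − Φ(0.875) = 19.1% | 1 − Φ(1.305) = 9.6% |
| 10 | 1 − Φ(0.625) = 26.6% | 1 − Φ(1.055) = 14.6% |

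*Removed by t3 (simulation, 1 million per arm, no benefit of referral).* Control 8.9-23.4%, or 5-14 of 60; intervention 4.5-13.2%, or 3-8 of 60. The plan allows for 60 − 48 = 12 dropouts per arm from all causes.

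*Shrinkage of the between-arm difference*, relative to keeping everyone in the same scenario:

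| Measure | Referral has no benefit | Referred women improve by 3 points (assumed) |
|---|---|---|
| t1, mean and proportion | none | none |
| t2, mean | about 3-11% | about 0-4% |
| t3, mean | about 6-20% | about 1-9% |
| t3, proportion above 12 | about 12-37% | about 3-22% |

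With no benefit of referral, the mean difference under full retention is 1.68-1.71 points. At t3 it falls to 1.53-1.59 (25% diagnosed) or 1.37-1.46 (50%). The standard error with 60 per arm is 4 × √(2/60) = 0.73, so the largest loss, about 0.35 points, is under half a standard error.

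*No true effect.* With equal diagnosis probabilities, removal produces essentially no difference: within 0.02 points on the mean and 0.15 percentage points on the proportion.

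**The case against.** The strongest reply is that the plan's own account of conduct points away from removal. Risk management says what happens above 12: referral. It mentions no withdrawal and no end to follow-up, it expects the EPDS at every assessment, and the only exit it describes is the woman's own choice. The criterion may be a clumsy screening rule or a stop-and-refer safety rule. This stands: an intention to delete randomised women is not shown. What remains is that the item is printed as an exclusion, without a time limit, and no sentence says that these women stay.

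Second, a reader might infer a flat contradiction with a defined ITT analysis. The documents do not support that. ITT is invoked only for missing data, and if diagnosis merely ended follow-up, the later scores would be missing data within that sentence's scope. The analysis set may be in a statistical analysis plan that is not shown. The conflict is with the principle, and it is direct only if women are dropped from the analysis.

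Third, a diagnosis is not an EPDS score, and nothing says that psychologists report diagnoses back to the trial. The link through referral is plausible but inferred.

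Fourth, removed women will have been referred for care, so assuming no benefit gives the upper figures. This is right, and both columns are shown for that reason.

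**Conclusion.** The point holds as a defect of wording with a real but conditional consequence. Followed literally, the criterion takes randomised women out after an event bound up with the primary outcome, and the protocol does not say that they are retained.

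Under the assumptions above, the bias runs toward no difference. At six months it is about 6-20% of the mean difference and 12-37% of the difference in case proportion if referral does nothing, or about 1-9% and 3-22% if referred women gain 3 points. The effect on the mean is modest; the effect on prevalence, which the abstract names as the target, is larger. The diagnosis share, SD, means, correlations and benefit of referral are all assumed.

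A reader might go further and infer that the rule could create a false benefit. That needs diagnosis rates that differ by arm. Referral uses the same cut-off in both arms. Table 1 does teach only intervention women to assess their own depression status, but that is thin support for a difference, and the documents give no figure for one. A reader might also infer that scores obtained before the diagnosis would be deleted; no text supports that.

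**What to change.** Reword the criterion so that a diagnosis of postpartum depression or other severe mental illness excludes a woman only if made before randomisation. Then add a short statement covering three things:

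- A later diagnosis is a reason for referral and, in weeks 1-6, for stopping the App modules if clinically needed.
- All referred or diagnosed women stay in t1-t3 follow-up and are analysed in their allocated arm.
- Diagnoses are reported by arm.

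The referral rule itself stays unchanged.

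The cost is one reworded criterion and a few added lines. The downside is that women under a psychologist's care are asked to keep completing surveys, and some may decline. If retention was always the intention, the change only puts it in writing.

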### Measures

Measurements will be obtained at baseline (t_o_), immediately after the last intervention (t_1_), 3 months following the intervention (t_2_) and 6 months following the intervention (t_3_). The baseline data is collected when participants are enrolled, and after that, the data collection process will be implanted in the evaluation module of the mobile App. The primary outcome will be depression status. The secondary outcomes will be negative emotion symptoms including depression, anxiety and stress, parenting confidence. These will be measured as follows:*Demographic and Socioeconomic factors:* the information about Risk factors will be collected by demographic questioner including pregnancy and birth history, obstetric complications, delivery mode, baby gender, baby weight, baby health status, feeding pattern, satisfaction with family care, major life events. The socioeconomic factors include maternal age, marital status, history of depression, family history of mental disorder, occupation, medical insurance, education level, family income, and religious belief.*Depression status:* We will use the Edinburgh Postnatal Depression Scale (EPDS) Chinese version to assess participant’s depressive status, as this scale is an effective self-screening tool for PPD. The EPDS to be used in this study was translated by Lee [35] the sensitivity was 82%, the specificity was 86%, the positive predictive value was 44%, and the negative predictive value was 97%. The scale includes 10 items. The recommended threshold is < 9: no depression; 9 is regarded as a probable case; and 13 or more as suspected depression.*Negative emotion symptoms:* We will assess negative emotion symptoms using the Depression, Anxiety and Stress Scale (DASS-21), which is a self-report measure of anxiety, depression and stress levels used in diverse settings developed by Lovibond [36]. The Chinese version of DASS-21 was developed by Taouk ^[40]^ in 2001. This version was tested in Australian-Chinese speaking samples and Hong Kong-Chinese speaking samples, and indicated that the items had been adequately and appropriately translated and adapted. Wen Yi et al. [37] tested DASS-21 in 730 Chinese adults (over 18 years old), the result showed that the Cronbach’s α was 0.912 and the test-retest Pearson correlation coefficient was 0.751.*Parenting competence:* Parenting competence will be assessed using the Chinese version of Parenting Sense of Competence Scale (C-PSOC). The initial Parenting Sense of Competence Scale was an English version developed by Gibaud-Wallston [38]. In 2014 Chinese researcher, Yang Xiao translated it into Chinese and applied to Chinese population. C-PSOC includes efficacy and satisfaction factors and has 17 items. The Cronbach’s coefficient, efficacy factor and satisfaction factor of C-PSOC were 0.82, 0.80 and 0.85 respectively [39].

### Conditions

#### The intervention condition: app-based CBT

App-based CBT is comprehensive App that including investigation and intervention. The investigation section includes four surveys (baseline, immediately after the intervention, three months after the intervention and six months after the intervention). The content of investigation is mentioned in the measures section. Taking into account the needs for women to rest and care for their newborns after giving birth, in order to ensure the effectiveness of the intervention, our research team conducted a survey of the needs of mental health services for postpartum women before determining specific interventions. Based on this result, we developed intervention program. The intervention consists of six modules, participants need to complete one module each week for six consecutive weeks, and each module will takes an average of 30–40 min. Participants will receive a reminder if they haven’t started reading the content of each module for the fourth day after the module is opened. Module 1 (prologue) will help participants to gain a preliminary understanding of postpartum depression. Module 2 (emotion) will help participants understand the negative emotions and identify them. Module 3 (recognition) will assist participants recognize the erroneous thinking. Module 4 (amendment) will provide some strategies for participants to deal with the biased habitual thinking. Module 5 (rebound) will help participants focus on the present life and avoid immersing in negative emotions. Module 6 (remain happiness) will help participants review the techniques of emotion management and getting rid of biased thinking, so that they can keep happy (Table 1).

**Table 1 Tab1:** The conditions between intervention group and control group

Time	Intervention group	Control group
1 week	Prologue will help participant to understand the postpartum depression a. Using examples to introduce what is postpartum depression, PPD symptoms, and how to differentiate PPD with the normal changes which might happen after delivery b. New progress of the treatment and intervention of PPD c. Skill learning: Self-evaluate the status of PPD	a. Postpartum perineum incision care or caesarean section wounds; b. Explanation of lochia postpartum; c. Prevention of postpartum constipation
2 week	Emotion will help participants a. Understand what negative emotions is. b. Record negative emotions and the corresponding behavioral responses c. Skill learning: think differently	Neonatal feeding (breast feeding or bottle feeding) a. Encourage breastfeeding, and how to breastfeeding correctly. b. Identify situations that require bottle feeding
3 week	Recognition will assist participants understand a. What is the biased habitual thinking? b. What is the relationship between biased habitual thinking and negative emotions? c. Skill learning: identify the biased habitual thinking.	Neonatal care (bathing and touch) a. Time, temperature and supplies of bathing; b. Navel nursing c. Neonatal touch method
4 week	Amendment will provide some strategies for participants to deal with the biased habitual thinking a. Using example to help participants understand what is the consequences of the biased habitual thinking. b. How to divert their attentions from the troublesome thing. c. Skill learning: introspect your thinking.	Postpartum recovery (early training) a. The timing and frequency of getting out of bed b. Intensity of postpartum exercise
5 week	Rebound will help participants focus on the present life and avoid immersing in negative emotions. a. Record the daily life b. Balance your life c. Skill learning: Set short-term goals and long-term goals and	neonatal vaccination a. Knowledge of infant vaccination
6 week	Remain happiness will help participants a. Review the techniques of emotion management and getting rid of biased thinking b. Skill learning: Record the daily happy things	postpartum reproductive health (contraception) a. Choice of contraceptive methods

#### Control condition

Participants in control group will also complete six health education modules which are formulated according to the standard of health management service postpartum and the child health management through the App. It mainly includes the care of postpartum perineum incision and caesarean section wounds, breast or bottle feeding, postpartum recovery, neonatal care (bath and touch), neonatal vaccination and postpartum reproductive health (contraception) (Table 1).

### Sample size

A power analysis was performed for linear regression using University Dusseldorf G*Power 3.1 to determine the sample size necessary for analysis. The main objective of this study is to assess the effectiveness of App-based CBT on PPD high-risk mothers. According to previous studies, an effect size of 0.43 will be adopted [40]. The power analysis based on the conventional significant alpha level of 0.05 and a power of 0.90 using a two-tailed test. We calculate that the sample size required is 48 in each group. Considering a 20% dropout rate, the recruited sample size required in each group is 60.

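### The stated inputs (effect size 0.43, two-tailed 0.05, 90% power) do not give 48 per group for the visit-by-visit group contrasts; if 0.43 is a standardised mean difference, power is about 55%

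*Protocol article*

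**What the plan says.** The Sample size section gives the following.

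- Method: "A power analysis was performed for linear regression using University Dusseldorf G*Power 3.1". The number of predictors and any covariate correlation are not given.
- Effect: "an effect size of 0.43 will be adopted", attributed to earlier work. The metric (standardised mean difference, f, f-squared, r) is not named.
- Error rates: "The power analysis based on the conventional significant alpha level of 0.05 and a power of 0.90 using a two-tailed test".
- Result: "We calculate that the sample size required is 48 in each group".
- Dropout: "Considering a 20% dropout rate, the recruited sample size required in each group is 60". The abstract gives the matching total of 120.

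The Analysis section describes the comparison to be made: "We plan to analyse contrasts between intervention and control groups at baseline, post intervention, 3 months and 6-months follow-up". I read this as comparisons between arms at each visit.

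**The concern.** Alpha, power, sidedness and effect size are all printed, so the result can be checked apart from the unstated metric. An effect of 0.43 standard deviations is moderate, and a two-arm trial with 90% power for it normally needs well over 100 per arm. A figure of 48 is less than half of that.

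The recruitment target rests on this calculation. If 0.43 is a standardised mean difference, the article promises a 10% risk of missing its own planning effect, while the comparison it describes carries a risk of about 45%. A non-significant result could then be given more weight against the App than the design can bear.

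**Working it through.** **Inputs.** From Sample size: effect 0.43, two-sided alpha 0.05, power 0.90, 48 evaluable per group (96 in total), 20% dropout. From Analysis: intervention against control at each visit. Assumption: equal allocation, as the equal group sizes imply.

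**Dropout step.** 48 / (1 − 0.20) = 60 per group, 120 in total. This reproduces, so the question is the 48.

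**Reading A: 0.43 is a standardised mean difference d (assumption).** Unadjusted comparison at one visit.

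- Normal approximation: n per group = 2(1.960 + 1.282)² / d² = 2 × 10.507 / 0.1849 = 113.7, so 114. The noncentral t distribution gives 115.
- With 20% dropout: 115 / 0.8 = 143.75, so 144 recruited per group.
- Power at 48 per group: noncentrality 0.43 × √(48/2) = 2.107 on 94 degrees of freedom, power 55.0%.
- Power if all 60 per group are retained: 64.7%.
- Detectable difference at 48 per group: d = 0.67 for 90% power, d = 0.58 for 80%.

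Looser error rates do not produce 48 either:

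| Sidedness | Power | n per group |
|---|---|---|
| two-sided | 90% | 115 |
| one-sided | 90% | 94 |
| two-sided | 80% | 86 |
| one-sided | 80% | 68 |

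Calling the analysis a linear regression changes nothing by itself. Regressing the outcome on a 0/1 arm indicator is the same test: 230 in total for 90% power, and 55% power at 96.

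**Reading B: 0.43 is a regression-type effect size for the arm.** One predictor, two-sided 0.05, 90% power. With equal groups, d = 2f and f² = r²/(1 − r²).

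| 0.43 read as | Implied d | Total N needed | Power at 96 |
|---|---|---|---|
| f | 0.86 | 59 | 98.6% |
| r (standardised slope) | 0.95 | 49 | 99.6% |
| f-squared | 1.31 | 27 | over 99.9% |

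None gives 96 in total, and at 96 the power is not 90%.

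**Reading C: d = 0.43 with a more efficient model.** Regress the mean of the three follow-up scores on arm and baseline. With correlation r_f between follow-ups and r_b between baseline and each follow-up, and equal variances, the variance factor relative to one unadjusted visit is

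V = (1 + 2r_f)/3 − r_b².

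The effective standardised difference is 0.43/√V.

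| r_b | r_f | V | Power at 48 per group |
|---|---|---|---|
| 0.5 | 0.5 | 0.417 | 89.8% |
| 0.3 | 0.5 | 0.577 | 78% |
| 0.2 | 0.5 | 0.627 | 75% |
| 0.3 | 0.6 | 0.643 | 74% |
| 0.2 | 0.6 | 0.693 | 71% |

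For r_b = r_f = 0.5 the normal formula gives 113.66 × 0.417 = 47.4, so 48 per group. The correlations are illustrative; the article gives none.

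**The case against.** The best defence has two parts.

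First, the article never says that 0.43 is a standardised mean difference, and it names linear regression. A reader might infer from the 55% figure that the trial is simply underpowered. The document does not support that as a flat statement: under f, r or f-squared the same 96 women would have over 98% power. This stands, and it makes the 55% conditional. It does not rescue the calculation, because under those readings too the inputs and the 48 per group disagree.

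Second, a regression on baseline with the three follow-ups averaged reaches about 90% at 48 per group with d = 0.43 and a common correlation of 0.5. So it would be wrong to say that no sensible model gives 48, or that only a very strong baseline correlation could. That stands as a matter of arithmetic. However, the Sample size section states neither the averaging nor a correlation, and the Analysis section lists contrasts by visit. Eligibility also confines baseline EPDS to 9–12, which would tend to lower the baseline correlation; at 0.2–0.3, with follow-up correlations of 0.5–0.6, power is about 71–78%.

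A reader might also infer how the error arose, for instance from a total of 49 written as a per-group figure. The match is not exact and nothing in the document confirms it, so no weight should be put on it.

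The condensed format of an article is not an answer. This is a printed result with its inputs, not an omitted detail.

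**Conclusion.** The sample size statement is wrong as written: for an unadjusted arm contrast at a single visit, no reading of 0.43 considered here as the arm effect yields 48 per group at 90% power. That disagreement does not depend on the metric.

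The size of the shortfall does. On the standardised-mean-difference reading, an unadjusted single-visit contrast has about 55% power instead of 90%, and 48 is about 42% of the 115 evaluable per group required (48/115). With baseline adjustment and averaged follow-ups the gap could be much smaller or nearly vanish, depending on correlations the article does not state. I am confident of the mismatch and moderately confident that 55% is the relevant power.

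**What to change.** Keep the recruitment target and rewrite the paragraph.

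1. State the metric of 0.43.
2. State the model behind the calculation: which visit or visits, whether baseline is a covariate, and any correlation assumed. It should match the between-group contrast actually planned.
3. Redo the calculation for that contrast and replace the 90% claim with the power or detectable difference it gives.

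If the contrast is unadjusted at one visit, suitable wording would be: with 48 evaluable women per group, a two-sided 5% comparison has 90% power for a standardised mean difference of 0.67, 80% for 0.58 and about 55% for 0.43. If a baseline-adjusted mean of the follow-ups is intended, say so, give the correlations, and show power over a plausible range of them.

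The cost is one paragraph and no extra participants. The stated power becomes less favourable.
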